### Patient safety

#### Adverse events

Adverse events are undesirable signs or symptoms that occur during the study and may or may not be causally related to the treatment. All adverse events considered possibly, probably or definitely related to the tested product will be recorded on CRFs.

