### Study schedule and location

After inclusion, all further treatments will be managed at the primary care center where the subject was recruited (see Table 1 for scheduled visits). A research nurse and a research dietician will be responsible for all contacts with patients. Doctors associated with the research team will be available if problems arise.

**Table 1 T1:** Schedule of visits

	**Pre-screening**	**Screening**	**Inclusion**	**Week**				
				**0**	**4**	**8**	**12**	**26**
Patient attends the health clinic		X		X		X	X	X
Telephone review					X			
Identification of eligible subjects	X							
Check eligibility		X						
Obtain informed consent			X					
Blood sampling				X		X		X
Stool sampling				X		X		X
Provision of test product				X		X	X	
Return of previously provided test product						X	X	X
Assessment of compliance and adverse events					X	X	X	X

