#### Serious adverse events

Serious adverse events are defined as events that are fatal, life-threatening, disabling, incapacitating or result in hospitalization or prolonged hospital stay, or result in malformation. All will be recorded in the CRF, whether they are related to the test product or not. According to previous studies [9], probiotics are safe, and any serious adverse event that might be possibly, probably or definitely related to the test product will be regarded as unexpected. All unexpected serious adverse events will be reported immediately to the Medicines and Healthcare products Regulatory Agency. Any serious adverse event that might be related to the tested product will immediately lead to discontinuation of the test product.

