### Plan for data analysis

As this trial is designed to assess the physiological effects rather than support clinical indications for treatment with probiotic**s** in T2DM, we plan to perform per protocol analyses. Only subjects treated with at least 80% of the planned doses for at least 80% of the time will be considered as treated per protocol.

Raw data will be entered into statistical software (SPSS version 16.5, Chicago, IL, USA). Preparation of the dataset will be done prior to analysis. Descriptive statistics will be performed, and frequencies will be presented as a percentage. Continuous variables will be presented as mean ± SD. Variables exhibiting non-Gaussian variables will be transformed prior to analysis. Repeated measures analysis of co-variance will be used to compare groups, which will represent a combination of analysis of variance and linear regression. Confounding and fixed variables such as age and gender, as well as body mass index, will be taken if proper matching has not been achieved prior to repeated measures. *Post hoc* Banjamini-Hohberg corrections will be done for multiple comparisons. For comparison of two groups, an independent *t*-test will be applied for continuous variables and Mann–Whitney for non-continuous variables. Analysis of adverse events (if any) will be performed using Chi-Square test and Fisher’s exact test following assumptions of randomness, independence and size. Significance will be set at *P* < 0.05.

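### Non-serious adverse events reach the CRF only if judged product-related, so the planned comparison between arms runs on pre-screened data that cannot be restored later

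*Protocol article*

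**What the plan says.** All references are to the Protocol article.

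- **Adverse events (definition).** The definition does not depend on cause: "Adverse events are undesirable signs or symptoms that occur during the study and may or may not be causally related to the treatment".
- **Adverse events (recording).** The next sentence sets the recording rule: "All adverse events considered possibly, probably or definitely related to the tested product will be recorded on CRFs".
- **Serious adverse events.** The rule here is the opposite: "All will be recorded in the CRF, whether they are related to the test product or not". Reports go to a named agency: "All unexpected serious adverse events will be reported immediately to the Medicines and Healthcare products Regulatory Agency".
- **Data handling and record keeping.** The research nurse completes the CRF and enters its data into the electronic database.
- **Table 1.** The row "Assessment of compliance and adverse events" is marked at weeks 4, 8, 12 and 26.
- **Plan for data analysis.** The section opens by choosing per-protocol analyses, on the ground that the trial studies physiological effects. It names no other set. Its second paragraph adds: "Analysis of adverse events (if any) will be performed using Chi-Square test", with Fisher's exact test alongside. That sentence names no analysis set.

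**The concern.** In a randomised, double-blind trial, comparing all events by arm shows whether the product causes harm without anyone having to attribute each event. The recording rule puts individual attribution before that comparison. Non-serious events judged unrelated are not required on the CRF, so they need not reach the database or the test.

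The events most exposed are those nobody expects the product to cause, because they are the ones most readily judged unrelated. If such events occurred more often on one arm, the planned test could miss the difference. An analysis plan written later can choose sets and methods, but it cannot bring back events that were never written down. This is therefore not a detail that can be left to an unseen document.

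**Working it through.** **Step 1: the passages side by side.**

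| Item | Rule in the protocol | Depends on judged cause? |
|---|---|---|
| Definition of adverse event | Any undesirable sign or symptom during the study | No |
| Serious event on the CRF | All | No |
| Non-serious event on the CRF | Only if judged at least possibly related | Yes |
| Test between arms | Chi-square or Fisher on adverse events | Inherits the CRF rule |

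The two recording rules stand in adjoining sections and are worded in opposite ways, so the filter reads as a rule and not as loose drafting. Table 1 fixes when events are assessed; it does not change which are recorded.

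**Step 2: what the filter does to power.** The protocol gives no expected event rate and no power for safety, so there is no figure of its own to reproduce. The following is an illustration.

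Inputs:
- n = 60 per arm (Design section).
- Two-sided 0.05 (Plan for data analysis gives the 0.05 level; two-sided is taken from the Sample size section).
- True any-event rates of 45% and 25%: an assumption, not in the protocol. The background is then 25 points and the excess 20 points.

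Formula (normal approximation): power = Φ[(|p1 − p2| − 1.96·se0) / se1], where se0 = √[2·p̄(1 − p̄)/n], se1 = √[(p1(1 − p1) + p2(1 − p2))/n], and p̄ is the mean of p1 and p2.

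Unfiltered: p̄ = 0.35, se0 = 0.0871, se1 = 0.0851. (0.20 − 1.96 × 0.0871)/0.0851 = 0.344, so power is 63.5%.

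*Pattern A: the filter removes the same share of every kind of event in both arms.*
- Half kept: 22.5% vs 12.5%; se0 = 0.0694, se1 = 0.0688; z = −0.523; power 30.0%.
- One third kept: 15% vs 8.3%; se0 = 0.0586, se1 = 0.0583; z = −0.827; power 20.4%.

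*Pattern B: the filter removes only background events and keeps the whole excess.*
- Half the background removed (12.5 points per arm): 32.5% vs 12.5%; se0 = 0.0762, se1 = 0.0740; z = 0.683; power 75%.
- Two-thirds removed (25 × 2/3 = 16.7 points per arm): 28.3% vs 8.3%; se0 = 0.0706, se1 = 0.0682; z = 0.902; power 82%.

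Under these two patterns power runs from about 20% to about 82%, against 64% with everything recorded. Neither pattern is a bound. If the excess itself is what gets judged unrelated, the recorded rates become equal and the test cannot show the difference at all. The protocol gives nothing that would say which pattern applies.

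**Step 3: the analysis set.** The per-protocol definition asks for at least 80% of doses for at least 80% of the time: 0.80 × 26 = 20.8 weeks. A patient who stops well before that leaves the only set named; one who stops later may stay in it. Whether that set governs the adverse event test is not stated.

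**The case against.** The strongest reply is that the filter is mild and much of the safety picture lies outside it.

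- The threshold is low, since a possible relation is enough. Gut complaints on an oral gut product would plausibly pass it.
- Serious events are recorded whatever their cause.
- Glucose, HbA1c and transaminases are measured, and medication changes recorded, irrespective of causality.
- A filter that removes mainly background noise can sharpen a comparison, as pattern B shows.
- The trial is presented as physiological, its sample size rests on endotoxin, and it states no safety hypothesis.

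All of this stands and limits the point. It does not remove it: the non-serious events judged unrelated still go unrecorded, and the protocol still plans a test between arms on what is left.

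A reader might also infer three stronger things that the documents do not support.

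1. *That the filter favours the probiotic.* Patients and clinicians are blinded, so nothing shows that relatedness is judged differently by arm. The protocol's remark on the safety of probiotics serves to class related serious events as unexpected; it is not an instruction for judging non-serious ones.
2. *That safety is analysed per protocol, so patients who stop because of harm are dropped.* A possibly related serious event "will immediately lead to discontinuation of the test product", and early stopping can breach the 80% rule. But the stated reason for per-protocol analysis concerns physiological effects, the adverse event sentence names no set, and a safety set may stand in a fuller document.
3. *That power is certainly lost, or that a clean safety result would be an artefact.* Step 2 shows that power can move either way. The most that can be said is that such a result could be misleading.

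**Conclusion.** The point holds for the recording rule. For non-serious events, the planned comparison rests on data already screened by individual causality judgement, and an unanticipated excess judged unrelated could be missed beyond recovery. This follows from the text alone and needs no assumption.

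The size cannot be fixed from the documents. The 20% to 82% range against 64% rests on assumed rates of 45% and 25%, all 60 patients per arm, a normal approximation and the two filter patterns shown. It demonstrates that the direction is undetermined and does not estimate a loss. Bias between arms is possible but not shown, and use of the per-protocol set for safety is a possible reading that the text does not state. It should be fixed, but it does not by itself undermine the trial.

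A separate and smaller matter is the reporting route. Serious event reports go to the Medicines and Healthcare products Regulatory Agency, a UK body, while the Design, Recruitment and ethics sections describe a single-centre trial recruiting in Riyadh under King Saud University ethics review, with no UK site mentioned. These passages must be reconciled. The mismatch has no bearing on the filtered-data point.

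**What to change.** 1. In the Adverse events section, have every adverse event recorded on the CRF regardless of suspected cause, with the blinded relatedness judgement as a separate field. Related events can still be tabulated on their own, so nothing the present rule offers is lost.
2. In the Plan for data analysis, state that adverse events are compared in all randomised patients who took at least one sachet. This removes the possible reading that the per-protocol set applies to safety.
3. Reconcile the agency named for serious event reports with the trial's stated location and ethics oversight.

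The cost is slightly more data entry at the contacts already scheduled for weeks 4, 8, 12 and 26, and some changes of wording. The first change has to be in place before events are collected, because those left off the CRF cannot be reliably reconstructed.

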#### Serious adverse events

Serious adverse events are defined as events that are fatal, life-threatening, disabling, incapacitating or result in hospitalization or prolonged hospital stay, or result in malformation. All will be recorded in the CRF, whether they are related to the test product or not. According to previous studies [9], probiotics are safe, and any serious adverse event that might be possibly, probably or definitely related to the test product will be regarded as unexpected. All unexpected serious adverse events will be reported immediately to the Medicines and Healthcare products Regulatory Agency. Any serious adverse event that might be related to the tested product will immediately lead to discontinuation of the test product.

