
## Methods

### Design

In this 26-week, single-center, double-blind, randomized, placebo-controlled study, 60 patients with T2DM will be treated with probiotics and 60 will be treated with placebo. Interventions will be performed at weeks 0, 4, 8, 12 and 26 in all subjects. Patients allocated to the probiotics group will receive two sachets with 2 g freeze-dried powder of the probiotic mixture Ecologic®Barrier daily (Winclove probiotics, the Netherlands). Ecologic®Barrier (2.5 × 10^9^ cfu/gram) contains the following bacterial strains: *Bifidobacterium bifidum* W23, *Bifidobacterium lactis* W52, *Lactobacillus acidophilus* W37, *Lactobacillus brevis* W63, *Lactobacillus casei* W56, *Lactobacillus salivarius* W24, *Lactococcus lactis* W19 and *Lactococcus lactis* W58. Participants in the placebo group will receive the placebo consisting of the carrier of the probiotic product, that is maize starch and maltodextrins. The placebo is indistinguishable in color, smell and taste from the probiotic sachets, but contains no bacteria.

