### Recruitment of patients

Recruitment of patients to this study will be made possible by collaboration with primary care centers throughout Riyadh and the Biomarkers Research Program, College of Science, King Saud University.

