### Ethical approval

The study protocol has been approved by the ethics committee of the College of Science, King Saud University, Riyadh, Saudi Arabia.

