### Ethical and regulatory aspects

The study will be performed in accordance with the protocol and the ethical principles that have their origin in the Declaration of Helsinki as well as with the International Council for Harmonization Guidance on Good Clinical Practice. These documents state that the informed consent of subjects is an essential precondition for participation in the clinical study. The study will commence only after obtaining approval from the local ethical review board of the College of Medicine Research Center, King Saud University.

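### The serious adverse event rule names only the UK medicines regulator as recipient, although the trial is recruited, treated and ethically overseen in Riyadh and nothing visible gives that agency a role

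*Protocol article*

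**What the plan says.** The section on serious adverse events contains one external reporting rule: every unexpected serious event is to be "reported immediately to the Medicines and Healthcare products Regulatory Agency". It also says what counts as unexpected: "any serious adverse event that might be possibly, probably or definitely related to the test product will be regarded as unexpected". No other outside recipient is named there or elsewhere in the article.

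The setting is described in other sections:

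- Recruitment of patients: "collaboration with primary care centers throughout Riyadh", together with a research programme at King Saud University.
- Study schedule and location: "all further treatments will be managed at the primary care center where the subject was recruited".
- Design: a "single-center, double-blind, randomized, placebo-controlled study".
- Ethical approval: the protocol has been "approved by the ethics committee of the College of Science, King Saud University, Riyadh, Saudi Arabia".
- Ethical and regulatory aspects: the study is to start only once approval is obtained from the "local ethical review board of the College of Medicine Research Center, King Saud University".

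**The concern.** This is an operative instruction that tells staff where a safety report goes. The agency it names is the medicines regulator of the United Kingdom, but the visible text describes no UK site, participants, sponsor or authorization. The bodies that do have a described oversight role, those at King Saud University, are not mentioned in the rule.

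Reports of serious events that may be caused by the product are what an outside body needs in order to judge whether the trial should continue for the remaining participants. Sixty of the 120 are to receive live bacteria for 26 weeks. If staff follow the sentence literally and nothing else instructs them, a related event in Riyadh is sent to an agency with no evident standing in the trial, and no one is told to notify the committee that approved it.

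**Working it through.** The point concerns text and not a figure, so there is nothing to recompute. The check sets the reporting rule beside the sections that describe where the trial is run and who oversees it.

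**1. Which events the rule covers.** Unexpected serious events go to the agency, and any serious event at least possibly related to the product counts as unexpected. Together these make the rule apply to every related serious event. Because the trial is double-blind, clinicians judge relatedness without knowing the arm. Reports could therefore come from any of the 120 participants (60 + 60), not only from the 60 on the active product.

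**2. Who receives the report.** One recipient is named. The article does not say that the agency is British, but that is simply what the agency is.

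**3. Where the trial takes place.**

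| Element | Section | Location or body |
|---|---|---|
| Recruitment | Recruitment of patients | Riyadh primary care centers |
| Treatment and follow-up | Study schedule and location | The recruiting center, so Riyadh |
| Participants | Abstract and Background | Saudi adults |
| Blood analysis | Acquisition of routine biochemical data; Recruitment of patients | A research programme at King Saud University |
| Product supply | Design | A company in the Netherlands |
| Ethics oversight | Ethical approval; Ethical and regulatory aspects | King Saud University |

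No row leads to the UK. The single-center label in the Design section sits awkwardly with recruitment across several centers, but neither description leaves room for a UK site.

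**4. Which local body would receive a report.** The article gives two answers. Under Ethical approval, a College of Science committee has already approved the protocol. Under Ethical and regulatory aspects, approval is still to come from a College of Medicine Research Center board. Adding a reference to the approving committee would therefore not identify a single recipient until these two statements are reconciled.

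**5. What the article already provides.** All serious events are recorded on the case report form, whether related or not. A possibly related one leads at once to discontinuation of the product. The investigator may withdraw a participant for safety reasons, and doctors linked to the research team are available. Local trial staff would therefore know of an event. What remains unaccounted for is notification outside the trial team.

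**The case against.** The strongest case on the other side has four parts.

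- **The rule is not exclusive.** It names one recipient and does not say that no one else is told. A journal article condenses a fuller protocol, and notifying the local committee is the kind of detail commonly left there. The article also commits the trial to Good Clinical Practice and to a local review board. This stands. A reader might infer that reports would bypass the bodies overseeing the trial, or reach none of them, and the text does not support that. It supports only the statement that no Saudi body is named.
- **A UK link may exist out of sight.** Title, signature and contact pages were removed, and a UK sponsor or collaborator could appear there. This also stands, as a limit: the agency's role is unexplained in what can be read, and is not shown to be absent.
- **People able to act would still know.** The recording and discontinuation provisions mean that the trial team is informed. This stands, and it confines the gap to outside notification.
- **Timing.** Asking for a reporting deadline would add little, since the rule already requires immediate reporting. This stands, and no deadline is requested here.

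None of this removes the central point. Silence on local reporting would have been no finding in a condensed article. This article is not silent: it fixes a recipient, and that recipient does not match the setting it describes. A fuller protocol that adds local reporting would not make this sentence fit.

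**Conclusion.** Wrong as written. The only named recipient of related serious adverse event reports is the UK regulator, for a trial whose visible text places recruitment, treatment and ethics oversight entirely in Riyadh. The reporting rule has to be reconciled with the sections on recruitment, study location, ethical approval and regulatory aspects.

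The rule applies to every related serious event among 120 participants. The article gives no serious event rate, so no expected number of reports can be stated. The issue does not touch the endpoint, sample size, randomization or analysis; its weight comes from participant safety and from how little it costs to correct.

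The conclusion rests on two assumptions: that no removed page gives the UK agency a formal role, and that the sentence in the article is the rule that staff will follow. If the first fails, the agency can stay, but its role still has to be stated. If the second fails because the full protocol names local recipients, the practical risk largely disappears and what is left is a misleading sentence in the published article.

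**What to change.** Amend the section on serious adverse events as follows:

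1. Settle which university body oversees the trial, the College of Science committee or the College of Medicine Research Center board, and make the two ethics statements agree.
2. Name that body as a recipient of the immediate report.
3. Name as a further recipient whichever authority has responsibility for the Riyadh sites. The article does not identify one, so the sponsor must.
4. Keep the UK agency only if it has a formal role in the trial, and say what that role is. Otherwise remove it.

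The cost is a short protocol amendment, the work of settling the ethics body, and the added reporting lines themselves. Design, sample size, treatment and analysis do not change.

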### Ethical and regulatory aspects

The study will be performed in accordance with the protocol and the ethical principles that have their origin in the Declaration of Helsinki as well as with the International Council for Harmonization Guidance on Good Clinical Practice. These documents state that the informed consent of subjects is an essential precondition for participation in the clinical study. The study will commence only after obtaining approval from the local ethical review board of the College of Medicine Research Center, King Saud University.

